- (3) Setting objectives. The SMART (Specific, Measurable, Achievable, Realistic, Time-based) objective was set for behavioral change as follows: “To increase the percentage of 40–79 years-old individuals who engage in aerobic, flexibility, and/or muscle-strengthening activities in an intervention group from 58% to 66% over a one-year period.” The baseline percentage was estimated from the available data for Unnan. A previous systematic review reported that the median net increase in the percentage of people who reported being physically active as a result of a CWC was 4.2% (range, -2.9% to 9.4%).[7] We decided on the 8% increase because the area and population sizes are relatively small in this study and the effect of a CWC is potentially greater within the community compared to a larger scale CWC (e.g., state or prefecture level).

(4) Marketing strategy development. A CWC follows the “4 Ps” concept of marketing mix (i.e., making sure the right *Product* is available at the right *Price*, in the right *Place* and is well-*Promoted*). Figure 3 shows the concept of marketing mix and examples of each component for promoting physical activity in this study. For example, when we think of *Product* (i.e., physical activity), the benefits of the product rather than the product itself are emphasized.[35] So rather than promoting physical activity *per se*, campaigns should promote ideas such as feeling good, having increased energy or longevity, according to the identified views of the target segments.[36] In the process of creating messages and materials, formative research is done, including interviews with target and other segments on their lives and values; further, pretesting of materials is done through interviews with the target segment about their feelings toward and impressions of such materials.

[figure not shown]

Figure 3: Concept of marketing mix and example elements of the four Ps for promoting physical activity in the COMMUNICATE study  
PA: physical activity

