## 5. Population-based evaluation

The effectiveness of the intervention will be evaluated using a population-based survey, which will be a prospective cohort design. As a baseline survey, self-administered questionnaires will be mailed to random participants, i.e., those who are randomly sampled using a computer-based resident registry system. Eligible participants will be all men and women aged 40 to 79 years living in the study areas (i.e., 12 communities). Those excluded are individuals in assisted living facilities, those who require long-term care, or those who cannot complete the questionnaires by themselves due to disability. We considered systematically reviewed effective methods to increase response rates,[39] and decided to incorporate the following recommended techniques, i.e., non-monetary incentives, university sponsorship, personalized and relatively short questionnaires, and assurance of confidentiality. We will also send postcard reminders to non-responders, add a preface from the Vice-Mayor to the front cover, make announcements by local audio broadcast and local cablecast, establish a call center for questions, and send a written request for cooperation to community leaders.

Both a one-year and three-year follow-up questionnaire survey from the conducting of the baseline survey is planned (Fig. 1). Follow-up questionnaires will be mailed to the respondents in the baseline survey. Surveys for mortality, functional independence (requirement of long-term care), and morbidity of specific diseases in successive years are also planned as future exploratory studies.

All respondents will give written informed consent to participate in these cohort surveys at the baseline survey. The content of the questionnaires will be the same for all residents. Both participants and data collectors will be randomly-sampled residents. Residents will be blinded to (not informed about) the study design and hypothesis (i.e., the existence of the control group and cluster allocation).[40] While the implementing staff of the CWC (intervention providers) and data analysts will not be blinded to the cluster allocation, the CWC collaborators (e.g., staff of each community's self-administered organization, Senior Citizens' Clubs, schools and clinics) will be blinded to (not informed about) the study design and hypothesis (the existence of the control group and allocations of other study communities). The Mayor, Vice-Mayor,

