## **6. Measures**

### *6.1. Primary outcome*

The primary outcome to be measured is the change in engagement in regular aerobic, flexibility, and/or muscle-strengthening activities from baseline to one-year follow-up. If respondents meet any one of the three following conditions, then they are defined as “engaging in regular physical activity”: (1) engaging in 150 minutes/week or more of walking, (2) engaging in daily flexibility activity, or (3) engaging in muscle-strengthening activities two or more days/week. The threshold of these conditions is based on the physical activity recommendations of the American College of Sports Medicine and the American Heart Association.[2, 23]

Total walking time for both recreation and transport is to be considered as engagement in walking (aerobic activity). Frequency of engagement in flexibility activity will be assessed categorically (daily, not daily but occasionally, not at all). Walking and flexibility items were adopted from the questionnaire used in the Shimane Study. Test-retest reliability (Spearman’s  $\rho=0.79$ ,  $P<0.01$ ) and validity, with average daily step counts recorded by a uniaxial accelerometer, (Spearman’s  $\rho=0.41$ ,  $P<0.01$ ) of walking times in the elderly population were acceptable.[34] The weekly number of days engaged in muscle-strengthening activity is to be assessed using a newly developed questionnaire asking “Do you usually do activities to maintain and/or improve muscles and/or muscle strength (e.g., sit-ups, squats, knee extensions)?” and by identifying the number of days in which they engage in these activities.

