## **7. Statistical analyses**

### *7.1. Sample size*

Based on available physical activity data for Unnan, the estimated rate of participation in regular aerobic, flexibility, and/or muscle-strengthening activities at baseline is 58% with an estimated intracluster (intraclass) correlation coefficient (ICC) of 0.00174. Groups A, FM, AFM, and the control group have equal sample sizes. The primary analysis is a comparison of the three intervention groups with the one control group. We obtained a sample size of 1,536 for the intervention groups and 512 for the control group, using the chi-square test by individual level, imbalanced [3 intervention; 1 control], a two-sided 5% significance level, and a power of 90% to detect an 8% difference in change in engagement in regular physical activity between the intervention and control groups (as described above in the social marketing section), without taking into account the design effect (DE) by the cluster randomization, as

follows:

$$n = \frac{\left( Z_{\alpha} \cdot \sqrt{(1+3) \cdot \frac{p_c + 3p_i}{1+3} \left( 1 - \frac{p_c + 3p_i}{1+3} \right)} + Z_{\beta} \cdot \sqrt{3 \cdot p_c(1-p_c) + p_i(1-p_i)} \right)^2}{3 \cdot (p_i - p_c)^2}$$

where

$p_i$  is rate of engagement in regular physical activity in intervention group

$p_c$  is rate of engagement in regular physical activity in control group

To retain power in the cluster randomized trials, the sample size should be multiplied by the DE, which is obtained as follows:[50]

$$DE = 1 + (\bar{m} - 1) \cdot ICC$$

where

$DE$  is design effect

$\bar{m}$  is the average cluster size

$ICC$  is intracluster (intraclass) correlation coefficient

If we plan to recruit an average of 500 participants in each cluster and assume a final sample of 250 in each cluster with a 50% response rate at baseline, the estimated DE is 1.44. The product of the obtained sample size of 512 in the control group and estimated DE of 1.44 is 738. Thus, recruiting nine clusters and 4,500 participants in the intervention groups and three clusters and 1,500 participants in the control group will retain expected statistical power. A total of 6,000 participants in the 12 clusters will be surveyed at baseline.

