## 7.2. Primary and secondary analyses

We will use cluster specific methods because communities rather than individuals (participants) are randomized and the data are to be collected at the individual level. For primary analysis, we will compare the nine intervention clusters to the three control clusters for the primary outcome of engagement in regular aerobic, flexibility, and/or muscle-strengthening activities at one-year follow-up using a generalized linear mixed model (GLMM) with sex, age, BMI,

self-rated health, years of education, employment status, engagement in farming, chronic low back and knee pain, chronic disease history, category of population density of each cluster, engagement in regular aerobic, flexibility, and/or muscle-strengthening activities at baseline, and group allocation (i.e., intervention or control) as fixed effects and community (cluster) where respondents live as a random effect.

As secondary analyses, we will compare the nine intervention clusters to the three control clusters to determine changes in VAS pain scores and chronic pain of low back and knee using a GLMM, adjusted for sex, age, BMI, self-rated health, years of education, employment status, engagement in farming, engagement in regular physical activity at baseline, chronic disease history, and category of population density. In addition to the comparison between all intervention groups and the control group, we will compare each intervention group (i.e., Group A, FM, and AFM) to the control group for primary and secondary outcomes and changes in engagement in each different activity (i.e., aerobic, flexibility, and muscle-strengthening activities) in the same manner using a GLMM.

As exploratory analyses, subgroup analyses will be conducted to detect significant differences in intervention effect, after stratification by sex, age group (40–59 and 60–79), and the market segment (primary communication target segment and the remaining population). Associations for engaging in physical activity, low back and knee pain (VAS scores and chronic pain), awareness of the campaign, and other obtained variables will also be analyzed as exploratory analyses.

We will assign cluster specific mean values to missing values. Significance will be set at  $P < 0.05$ . Analyses will be carried out using SAS version 9.1.3 and SPSS 14.0J.

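### The cluster-mean rule for missing values, as worded, also covers the yes/no one-year outcome and the pain outcomes, for which it is unsuitable

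*Protocol*

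**What the plan says.** Protocol section 7.2 sets out the primary, secondary and exploratory analyses and then states: "We will assign cluster specific mean values to missing values". The sentence does not say which variables it covers, whether it works on questionnaire items or on the derived outcome, or whether an unreturned one-year form counts as a missing value.

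Three other statements bear on it.

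- Section 6.1 makes the primary outcome yes/no: "If respondents meet any one of the three following conditions, then they are defined as" regularly active. The three conditions concern weekly walking minutes, daily flexibility activity (recorded in three categories) and days per week of muscle strengthening.
- Section 5 says "Follow-up questionnaires will be mailed to the respondents in the baseline survey". A person missing at one year has therefore normally reported baseline engagement.
- The primary GLMM in section 7.2 already includes "engagement in regular aerobic, flexibility, and/or muscle-strengthening activities at baseline, and group allocation (i.e., intervention or control) as fixed effects", with community as a random effect.

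Section 7.1 allows for 50% response at baseline but states no loss between baseline and one year.

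**The concern.** A single rule with no stated scope applies to everything, including the outcome. That raises three problems.

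1. **Validity of the filled value.** If the derived outcome is filled, the model receives a fraction where it needs 0 or 1. If the items are filled first, the outcome stays binary, but everyone in a community who lacks walking minutes or strengthening days falls on the same side of the threshold for that item. For flexibility, the mean of a three-level category is not a category.
2. **Loss of baseline information.** Everyone missing in a community receives the responders' average, whatever their own baseline status. If activity-related dropout differs between campaign and control communities, responders' averages shift by different amounts in the two arms, and the fill carries that shift into the treatment contrast.
3. **Variance.** Filled values have no spread within the cluster and are counted as data, so within-cluster variance is understated and the ICC overstated. This applies to the VAS outcomes as well.

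The primary contrast is at stake. The bias can go either way: exchanging the arms' dropout patterns reverses its sign.

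**Working it through.** **The plan's own yardstick.** Section 7.1 gives "the estimated rate of participation in regular aerobic, flexibility, and/or muscle-strengthening activities at baseline is 58" per cent, and section 4.1 sets the target as "from 58% to 66% over a one-year period". The design is "a two-sided 5% significance level, and a power of 90% to detect an 8% difference in change in engagement", allocated 3:1. The printed formula uses the pooled rate (0.58 + 3 × 0.66)/4 = 0.64:

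- 1.960 × √(4 × 0.64 × 0.36) = 1.8816
- 1.2816 × √(3 × 0.58 × 0.42 + 0.66 × 0.34) = 1.2525
- n = (1.8816 + 1.2525)² / (3 × 0.08²) = 511.6, that is 512

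This agrees with "We obtained a sample size of 1,536 for the intervention groups and 512 for the control group". The design effect is 1 + 249 × 0.00174 = 1.433 (stated as 1.44), and 512 × 1.44 = 737.3 (stated as 738). The 8-point target is therefore a sound yardstick.

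**Bias of the fill with no true effect.** The filled value equals the responders' mean. Let rA and rI be one-year retention of people active and inactive at baseline, and let a and b be their one-year activity rates.

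- Active share among responders: s = 0.58·rA / (0.58·rA + 0.42·rI)
- False effect = (s in intervention − s in control) × (a − b)

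Only the 58% comes from the protocol. The rest is assumed. The main case takes a = 0.80 and b = 0.276, so that 0.58 × 0.80 + 0.42 × 0.276 = 0.580 and the overall rate does not change.

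| Retention, intervention (active/inactive) | Retention, control | s, intervention | s, control | False effect, points |
|---|---|---|---|---|
| 85/65 | 85/65 | 0.644 | 0.644 | 0 |
| 80/70 | 80/80 | 0.612 | 0.580 | +1.7 |
| 85/65 | 80/80 | 0.644 | 0.580 | +3.3 |
| 85/70 | 75/85 | 0.626 | 0.549 | +4.0 |
| 85/60 | 75/75 | 0.662 | 0.580 | +4.3 |
| 90/60 | 80/80 | 0.674 | 0.580 | +4.9 |
| 90/65 | 75/85 | 0.657 | 0.549 | +5.6 |

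With a = 0.85 and b = 0.20, the last row becomes (0.657 − 0.549) × 0.65 = +7.0 points, the largest value examined. A 4-point false effect needs the active share among responders to differ between arms by 0.04/(a − b). That is about 6 points for 0.85/0.20, 7.6 for 0.80/0.276 and 10 for 0.75/0.35.

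**Does later adjustment for baseline remove it?** No. In simulated trials (12 clusters of 250, ICC 0.00174, individual-level linear model), the adjusted and unadjusted false effects after filling were within about 0.1 point of each other. The baseline coefficient fell from 0.52 to about 0.36–0.42.

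**Effect on the test.** These results are from 4,000 simulated trials per scenario, using a cluster-level t-test adjusted for baseline.

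| Scenario | Type I error, filled | Type I error, observed outcomes only |
|---|---|---|
| Same pattern in both arms | 5.2–5.5% | 4.9–5.6% |
| 80/70 v 80/80 | 8.6% | 4.9% |
| 85/65 v 80/80 | 22.6% | 5.0% |
| 85/70 v 75/85 | 30.9% | 4.5% |
| 90/60 v 80/80 | 42.3% | 5.0% |

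The baseline-adjusted analysis of observed outcomes had a false effect of 0.0 points (within 0.05) in all of these.

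**Variance.** Take a share f missing completely at random, m = 250 and ICC = 0.00174, in units of total variance. Then MSB = m·ICC + (1 − ICC)/(1 − f) and MSW = (1 − f)(1 − ICC). At f = 0.20, MSB = 0.435 + 1.248 = 1.683 and MSW = 0.799. The apparent ICC is (1.683 − 0.799)/(1.683 + 249 × 0.799) = 0.0044. An individual-level standard error is understated to (1 − f) of its true value, 0.8 here.

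**The case against.** **Scope.** The protocol never says outright that the one-year outcome is to be filled. The sentence could be meant for skipped items among people who return the form. That is fair: coverage of the outcome follows from wording without a limit. The item reading does not rescue the rule, for the reason given above. A separate statistical analysis plan might narrow it, but the protocol sentence is a fixed rule and not a detail left open.

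**Size.** A reader might infer that the rule creates a false effect of half the target. The documents do not support this. They give no one-year loss, no dropout by arm and no association between baseline and one-year activity. About 4 points needs strongly arm-specific dropout, such as a 25-point retention gap in one arm and none in the other, or opposite patterns. With equal patterns the bias is zero. Differential response is possible, since the campaign runs only in intervention communities, but residents receive the same questionnaire and are not told of the control group.

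**Rounding.** A reader might also suppose that filled means are rounded to 0 or 1, making every non-responder active. With 30% v 20% dropout this would give (0.58 × 0.70 + 0.30) − (0.58 × 0.80 + 0.20) = +4.2 points. The protocol has no rounding step, so this figure should not be relied on.

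**Variance.** Lower within-cluster and higher between-cluster variance offset each other when inference is at cluster level. Type I error stayed near 5% with equal dropout patterns, so harm to the primary test from this part alone is not shown.

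**The comparison.** The scenarios let dropout depend only on arm and baseline activity, which is where the adjusted observed-data model is unbiased. It is not protected if dropout depends on unobserved one-year activity. The simulations also used a linear model and a cluster-level test, not the planned GLMM.

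**Conclusion.** The point holds as a badly fixed rule. Followed as written, it gives the binary primary outcome either invalid fractions or uniform classes within a community, ignores baseline engagement that is normally known and already in the GLMM, and treats filled values as observed. None of this depends on a dropout assumption.

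The size of the bias does. It is zero with the same dropout pattern in both arms. It is about 1.7 to 5 points under moderate arm-specific patterns with one-year activity of 0.80 and 0.28, and up to about 7 points under the most extreme values tried. These should be read as a range against the 8-point target, not as a prediction. Under the same assumptions the planned covariate adjustment needs no fill.

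**What to change.** Replace the sentence in section 7.2 with wording such as:

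> Outcomes are not imputed with cluster means. The primary and secondary GLMMs are fitted to respondents with an observed one-year outcome, adjusted for the listed baseline covariates. Cluster-mean filling, if kept, applies only to missing baseline covariates. Sensitivity analysis: multilevel multiple imputation of the one-year outcome including arm, baseline engagement and the covariates, with a range of departures from missing at random applied separately by arm.

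The arm-specific departures address the case that the observed-data model cannot, namely dropout that depends on one-year activity itself.

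A single analysis that counts all non-responders as inactive should not be the main check. With 30% v 20% dropout and no true effect it gives 0.70 × 58% − 0.80 × 58% = 40.6% − 46.4% = −5.8 points.

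The cost is a few sentences of analysis text, a little extra programming and fewer records in the primary model. Data collection does not change.

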## **8. Data management**

Data acquisition and management will be conducted by the Physical Education and Medicine Research Center UNNAN.

For the data management, we will use ID numbers to identify the respondents. The information on the questionnaires will be entered into an electronic dataset along with the ID numbers of respondents, rather than their

actual names. The name-ID linkage file will be stored in a locked cabinet separately from the questionnaire dataset.

Regarding data analyses, the basic analyses (e.g., frequency distribution) will be performed by the researchers of the Physical Education and Medicine Research Center UNNAN (MK and JK). Primary and secondary analyses will be performed by the independent statistician (HN).

## **9. Ethical considerations, safety, and dissemination**

As described in Section 5, the effectiveness of the intervention will be evaluated using a population-based survey, which will be a prospective cohort design. All survey respondents will give written informed consent to participate in the cohort surveys at the baseline survey. The intervention will be implemented at community level, and the random-sampled respondents will not necessarily correspond to people who are aware of (or have received) the intervention. Respondents will not be informed about the study design and hypothesis (i.e., the existence of the control group and cluster allocation) and will only be informed about and asked for consent to participate in the cohort design consecutive surveys.

Before implementing the study, the protocol, informed consent, and questionnaires will be reviewed by the research ethics committee of the Physical Education and Medicine Research Center UNNAN. The committee also approves any amendments to the protocol, other than administrative ones. The questionnaire, which includes an informed consent form for the respondent, is appended to the protocol as Section 12.

During the intervention, the implementation core team will keep contact with each intervention community's self-administered organization, Senior Citizens' Club, schools and clinics. If the team obtains information about negative incidents thought to be caused by the CWC, e.g., a person who gets information about physical activity through the CWC and starts walking suddenly and consequently get worse knee pain, the team will immediately respond and modify the messages of the CWC.

The results of the study will be presented in academic meetings and journals by the study project members when appropriate. Any information concerning an individual that can identify a specific individual will not be presented anywhere.

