### *6.2. Secondary outcomes*

Low back and knee pain are to be evaluated as secondary outcomes. A visual analogue scale (VAS) from 0 mm (no pain) to 100 mm (most intense pain) will be used to assess pain intensity.[41] Additionally, chronic musculoskeletal pain is to be defined as current pain (i.e., an episode of pain during completion of the questionnaire) lasting longer than 3 months within the past 12 months.[42]

We will also evaluate awareness of the campaign for exploratory analysis. Awareness is to be evaluated based on a respondent's encounter with the following CWC components: (1) posters, leaflets, and banners, (2) local audio broadcasts, (3) mass - and individual- encouragement by health professionals during community-based medical check-ups and at community events, (4) individual encouragement by family, friends, and/or neighbors, (5) advice from physicians and medical staff in medical institutions.

Sociodemographic variables will include sex, age, body mass index (BMI) calculated from self-reported weight and height in  $\text{kg/m}^2$ , self-rated health (excellent; good; fair; poor), years of education, employment status (yes or no), and engagement in farming (yes or no). Most of these variables were considered to be related to physical activity.[43–46] Other information, including overall moderate to vigorous physical activity measured by the short version of the International Physical Activity Questionnaire,[47, 48] pain management, falls, psychological distress,[49] chronic disease history (e.g., heart disease, stroke, diabetes), and general health habits (e.g., smoking, drinking, participation in health education classes) will also be evaluated. Based on the information obtained by the questionnaire, those unable to walk unaided will be excluded from the analyses.

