1. ない 2. 右ヒザだけ 3. 左ヒザだけ 4. 両ヒザ

35. この1年間、ヒザやヒザのまわりが痛むことがありましたか？

1. ない 2. 右ヒザだけ 3. 左ヒザだけ 4. 両ヒザ

⇒あつた方にお尋ねします。そのヒザの痛みはどのくらい続きましたか(続いていますか)？

1. 7日未満 2. 1～4週間 3. 1ヶ月以上3ヶ月未満 4. 3ヶ月以上

⇒そのヒザの痛みは、現在も続いていますか？

1. はい 2. いいえ

36. この1年間、ヒザの痛みのために、受診することがありましたか？

1. なし 2. 1回 3. 2～6回 4. 7回以上

37. 次の線は、この数日間(ここ2、3日)のヒザの痛みの程度をおたずねするものです。

左の端を「痛みなし」、右の端を「最も激しい痛み」としたときに、この数日間のあなたの痛みの程度はどのあたりでしょうか？

線の上でこのあたりと思われるところに×印をつけてください。

|                                                          |
|----------------------------------------------------------|
| -----                                                    |
| 痛みなし これまでに経験した最も激しい痛み |

38. 現在、ヒザの痛みのために医薬品(飲み薬、湿布等)を使用していますか？使用している場合、何種類か数も書いてください。 ※サプリメントは含みません。

1. はい(\_\_\_\_種類) 2. いいえ

39. たばこを吸いますか？

1. 吸う      2. 以前吸っていた      3. 吸わない

1 日 \_\_\_\_\_ 本、 \_\_\_\_\_ 歳から \_\_\_\_\_ 年間

40. お酒(アルコール飲料)を飲みますか？

1. ほとんど毎日飲む      2. ときどき飲む      3. めったに飲まない

41. 憂鬱な気分になることがありますか？

1. はい      2. いいえ

42. 婚姻状況についてお答え下さい。

1. 既婚      2. 未婚

1. 同居      2. 別居      3. 離婚      4. 死別

43. 同居している家族はいますか？

1. はい      2. いいえ

44. 介護が必要な人と同居していますか？

1. はい      2. いいえ

45. 過去 1 年に転んだことがありますか？「はい」の場合、1 年間の転倒回数を記入してください

1. はい ( \_\_\_\_\_ 回/年)      2. いいえ

その転倒でケガや骨折はありましたか？「1. はい」の場合、わかる範囲でその部位を記入して下さい。

1. はい(部位: \_\_\_\_\_)      2. いいえ

46. 転倒をすることに対する恐怖感がありますか？

1. 全くない      2. あまりない      3. どちらかといえばある      4. 非常にある

47. 転倒を防ぐために、外出をひかえることがありますか？

1. 全くひかえない      2. ほとんどひかえない      3. 時々ひかえる      4. よくひかえる

48. 小学校入学から最終学歴まで、通算で何年間学校に通いましたか？

(専門学校・大学院は含みますが、予備校や留年・休学は除きます。)

例: 中学卒業まで; 9 年、高校卒まで; 12 年、

短大・専門学校卒業まで; 14 年、大卒まで; 16 年

年間

49. 現在、収入のある仕事のお時間はどのくらいですか？

週  日、1 日  時間

50. あなたは健康に関する教室や講演会、自治会行事、イベント、自主グループ等の活動に参加したことがありますか？あてはまる番号を1つ選んで○をつけて下さい。

- |                       |                   |           |
|-----------------------|-------------------|-----------|
| 1. 週に1回程度             | 2. 月に1～2回程度       | 3. 年に数回程度 |
| 4. 参加したことはないが参加したいと思う | 5. 参加したことはなく関心がない |           |

51. あなたは、肩・腰・膝などの痛みに対する対処法を見たり聞いたりしたことがありますか？

- |                                         |
|-----------------------------------------|
| 1. 医師等の専門家から聞いたり、医学専門書等の資料を読んだりしたことがある  |
| 2. テレビや雑誌等で見たり、あるいは、専門家ではないが人から聞いたことがある |
| 3. 見たり聞いたりしたことはない                       |

52. これまでに、医師に診断されたことのある疾患があれば、○をつけて下さい。

- |                                  |                              |             |
|----------------------------------|------------------------------|-------------|

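### Apart from low back and knee pain, the protocol specifies no between-arm comparison of possible harms over the campaign year, although falls and fall injuries are asked about in both arms

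*Protocol*

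**What the plan says.** Protocol section 9 says that during the campaign "the implementation core team will keep contact with each intervention community's self-administered organization, Senior Citizens' Club, schools and clinics". The trigger for action is "If the team obtains information about negative incidents thought to be caused by the CWC", and the response is that "the team will immediately respond and modify the messages of the CWC". The example given is a person who takes up walking abruptly and whose knee pain gets worse. Section 9 describes no count or tabulation of incidents. No matching contact with the three control communities is described; for these, section 4.2 records only the usual health services.

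Section 5 deals with the blinding of those who would hear of incidents: "While the implementing staff of the CWC (intervention providers) and data analysts will not be blinded to the cluster allocation". It also says that questionnaire content is the same for all residents. Surveys of mortality, long-term care need and morbidity are left to future exploratory studies.

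Section 6.2 lists low back and knee pain as secondary outcomes. Falls appear among the other information to be collected: "pain management, falls, psychological distress,[49] chronic disease history". In the appended questionnaire, item 45 asks whether the respondent has fallen in the past year ("過去 1 年に転んだことがありますか"), how many times, and whether injury or fracture resulted, with the site.

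Section 7.2 compares VAS pain and chronic low back and knee pain between the nine intervention and three control clusters with a mixed model, and again for each of Groups A, FM and AFM against control. Falls are not named. They are reached only by a closing line on exploratory associations among the remaining variables.

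**The concern.** A judgement about harm needs the same ascertainment in both arms. The section 9 route lacks this in three ways: it runs in the intervention communities only, it depends on staff who deliver the campaign and know the allocation, and it keeps only events attributed to the campaign. A fall that nobody links to a leaflet or a broadcast is not captured, and there is no control figure to set against those that are.

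Item 45 has none of these limits. It is put to both arms in the same words and asks for no opinion on cause. Its one-year recall, if the item is asked again at one-year follow-up, covers roughly the campaign year.

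Falls are a reasonable outcome to choose. The primary communication segments in section 4.1 are women aged 60–79 with low back or knee pain, and the campaign promotes walking, stretching and strengthening. The protocol does not itself name falls as an expected harm, but it does make light-reflective materials available for the safety of walkers.

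At stake is what the report can say about falls and injuries. Under the plan as written, the only material it commits to gathering for that purpose is one-arm and filtered by attribution. The data for a comparison would meanwhile sit unused, or be analysed without a stated plan.

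**Working it through.** **1. Which possible harms have a planned comparison by arm?**

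| Possible harm | Collected in both arms? | Between-arm analysis named? |
|---|---|---|
| Low back and knee pain (VAS, chronic) | Yes (6.2) | Yes (7.2) |
| Any fall, number of falls | Yes (6.2, item 45) | No; general exploratory line only |
| Injury or fracture from a fall | Yes (item 45) | No; general exploratory line only |
| Incidents heard of by the team | No; intervention communities only (9) | No |
| Death, long-term care need, morbidity | Later years (5) | Future exploratory studies |

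**2. The plan's own figures.** The protocol gives no figure for harms. Its sample size supplies the numbers of respondents and the design effect.

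- With 58% v 66%, two-sided 5%, 90% power and 3:1 allocation, the formula in section 7.1 gives 511.6, which rounds up to the stated 512 controls.
- DE = 1 + (250 − 1) × 0.00174 = 1.433 (stated as 1.44).
- Respondents: 9 × 250 = 2,250 intervention and 3 × 250 = 750 control.

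**3. Precision of a comparison of any fall.** The fall rates are assumptions, since the protocol gives none.

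SE = √[p(1 − p) × DE × (1/2,250 + 1/750)], where 1/2,250 + 1/750 = 0.001778 and 1.433 × 0.001778 = 0.002548.

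| Assumed p | SE | Half-width, 1.96 × SE | Half-width, 2.228 × SE (t, 10 df) |
|---|---|---|---|
| 10% | √(0.09 × 0.002548) = 0.0151 | 3.0 points | 3.4 points |
| 15% | √(0.1275 × 0.002548) = 0.0180 | 3.5 points | 4.0 points |
| 20% | √(0.16 × 0.002548) = 0.0202 | 4.0 points | 4.5 points |

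The 10 df come from 12 clusters less 2 arms.

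**4. Sensitivity to the ICC.** The value 0.00174 was estimated for physical activity, not falls. At an assumed ICC of 0.01, DE = 1 + 249 × 0.01 = 3.49. The half-width at 10–20% becomes 4.6–6.2 points with 1.96, and 5.3–7.0 with 2.228. Loss to follow-up, which these figures ignore, would widen every interval.

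**5. Detectable increase, 80% power, two-sided 5%, ICC 0.00174, normal approximation.**

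- Any fall, assumed control rate 10 / 15 / 20%: an increase of 4.8 / 5.5 / 6.0 points.
- Injurious fall, assumed control rate 1 / 2 / 3%: an increase of 2.1 / 2.7 / 3.1 points, that is a risk ratio of about 3.1 / 2.35 / 2.0. At 1–3%, only 750 × 0.01 = 7.5 to 750 × 0.03 = 22.5 control respondents would be expected to report one.

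A comparison of any fall would therefore be moderately informative. One of injurious falls would be imprecise.

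**The case against.** A reader might infer that the trial cannot tell whether the campaign does harm. The documents do not support that. Pain is measured alike in both arms and compared by mixed model, that comparison can show worsening, and worse knee pain is the harm section 9 gives as its example. A reader might also infer that falls will not be compared. The text shows only that no such comparison is specified, and the exploratory line does not exclude one.

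The stronger objections are these:

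- **Section 9 is a response rule, not an analysis.** Control communities have no campaign messages to modify, so its scope and attribution filter suit its purpose, and the protocol nowhere says that incident reports will be used to conclude safety. This stands. It is why the reports should be labelled descriptive rather than redesigned.
- **Naming a safety outcome can be left to the statistical analysis plan.** Details of model and tabulation can. Which collected variables count as outcomes is what section 6.2 sets out, and it places falls among background information.
- **Falls are the reviewer's choice of harm.** This stands in part. The campaign addresses ages 40–79, the promoted walking starts low, and the segment chosen for flexibility and strengthening already does such activity.
- **The precision is optimistic and serious injury stays unresolved.** This stands, and the working shows it.
- **Item 45 may not be repeated.** The appended form carries no wave label, and section 5 promises the same content across residents, not across surveys. This stands as an assumption to confirm.

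**Conclusion.** The concern holds in limited form. Low back and knee pain have a planned controlled comparison; other possible harms over the campaign year do not. Section 9 reports cannot supply a rate to compare, because there is no control count and events are selected by attribution. Falls and fall injuries are collected in both arms but are not tied to any specified comparison by arm.

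The gain from specifying one is an estimate of the difference in any fall to within about 3.0–4.0 points (normal multiplier) or 3.4–4.5 points (t on 10 df). This assumes a 10–20% fall rate, no loss from the 2,250 v 750 baseline respondents, the physical activity ICC, and item 45 being asked again at one year. With loss to follow-up or a larger ICC the interval is wider. Injurious falls would be estimated imprecisely, with three control clusters and few events.

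This is a cheap and worthwhile improvement. It does not affect the validity of the primary analysis.

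**What to change.** - **Section 6.2:** name any fall and any injurious fall (item 45) at one year as safety outcomes. State that item 45 is repeated in the one-year questionnaire, and label the appended form by survey wave.
- **Section 7.2:** report both outcomes by arm, nine intervention v three control clusters, with a cluster-adjusted difference and 95% confidence interval, adjusted for the baseline value. Use an interval method suited to 12 clusters, and make no significance claim.
- **Section 9:** say that incident reports are descriptive and are not a basis for a statement on comparative safety. The operational response to incidents need not change for this purpose.

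The cost is two further models on data already planned for collection, provided item 45 is in the one-year form. The downside is two more reported comparisons that rest on one-year recall and have limited precision. A wide interval for injurious falls should be reported as such and not read as absence of harm.
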